#### Process evaluation

A process evaluation conducted alongside the main trial will explore moderators of outcome and mediators of change. Candidate moderators include comorbid depression, disturbances in self-organisation, substance use, education level, gender, treatment credibility. Mediators of treatment outcome to be considered are processes hypothesised to maintain PTSD (problematic appraisals, memory qualities, maintaining behaviours such as rumination and thought suppression) and self-efficacy. Details will be specified in a separate statistical analysis plan.

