### Interventions

iCT-PTSD and iStress-PTSD will be delivered online via a series of therapy modules over 3 months, with the therapist support by messages within the programme, SMS and weekly phone calls (on average taking 4 h total of therapist time per participant). The therapist releases the modules gradually, two to three modules per week. Participants will retain access to the programme for a year post intervention and will be able to print and keep the therapy modules that they completed online. They will have up to three monthly phone calls with the therapist in the first 3 months of follow-up to help maintain treatment gains. Therapists will be experienced in cognitive behavioural therapy and will have received training in the delivery of both online treatments and have treated at least two supervised training cases in each condition.

The online treatments have the same user interface and design, and can be accessed by PCs, tablets or smart phones. Participants who do not have a PC or tablet will be able to borrow a tablet for the duration of treatment. Both interventions will be delivered via online modules that are identical in design and share the same multimedia features to facilitate engagement and accessibility (text with information and patient examples, videos of a therapist talking or whiteboard videos for key information, videos of patient testimonies, questions and text boxes for the patient to complete, audio-recordings for the patient to listen to, graphs and pictures). The modules and design were developed with extensive input from service-users. Therapists can, with the participant’s knowledge, read the information that the participant provides in the modules and can write notes for the participants directly into the modules.

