#### Wait-list

Participants allocated to the wait-list condition will receive assessments only at baseline, 6 weeks and 13 weeks, and will then be randomly allocated to iCT-PTSD or iStress if they still meet the criteria for PTSD. If they no longer have PTSD, their participation in the trial is finished.

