#### Treatment fidelity and credibility

Therapists will receive weekly group supervision for each of the treatment conditions to ensure adherence to the protocol and quality of treatment delivery. The iCT-PTSD supervision group will be led by [name], and the iStress-PTSD supervisor will be [name]. Therapists’ adherence to treatment components will be assessed by independent raters from messages therapists send via the online system and randomly selected audio-recordings of the phone calls between therapist and participant. Competence of delivery will be assessed by an independent clinical psychologist, using rating forms informed by the Cognitive Therapy Rating Scale-Revised [33]. Participants will be made aware of this in the participant information sheet. Credibility of treatments will be assessed with the self-report Borkovec and Nau’s Credibility Scale [34] in week 2 of treatment.

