### Allocation

After the eligibility assessment and giving informed consent for the trial, eligible participants will be randomised to one of the three trial conditions (iCT, iStress, wait-list) at a 3:3:1 ratio, stratified by location (Oxford, London, and Brighton and Hove), duration of PTSD (less than 18 months/18 months and above), and severity of PTSD symptoms on the PCL (high versus low), using an online random allocation programme developed by the Primary Care Clinical Trials Unit at the University of Oxford for this study. The programme uses a minimisation algorithm with a random component. The allocation sequence is not visible to the administrators who generate the treatment allocation with the programme.

For participants taking psychotropic medication, randomisation will take place after they have been on a stable dose for 1 month. For those currently receiving another psychological treatment, randomisation will take place after the end of this treatment. Participants originally allocated to the wait-list who have not recovered from PTSD at 13 weeks (end of wait) will be randomised to either iCT-PTSD or iStress at a 1:1 ratio.

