### Blinding

Assessors of treatment outcome will be blinded. Therapists supporting the Internet-based treatments, trial administrators and participants will not be blind to treatment allocation due to the nature of the intervention.

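### Treatment credibility is listed as a candidate moderator, but it is rated in week 2 of the assigned treatment, so an interaction with it cannot be read as effect modification by a pre-treatment characteristic

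*Protocol article*

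**What the plan says.** The Process evaluation section says the embedded study "will explore moderators of outcome and mediators of change" and keeps the two groups apart. For the first group it states: "Candidate moderators include comorbid depression, disturbances in self-organisation, substance use, education level, gender, treatment credibility". The other five entries are patient characteristics. Mediators are listed separately, and credibility is not among them. Details are left to a separate analysis plan.

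The section on treatment fidelity and credibility gives the only time point in the text for the rating: "Credibility Scale [34] in week 2 of treatment".

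Four other statements bear on that timing:

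- Allocation: "After the eligibility assessment and giving informed consent for the trial, eligible participants will be randomised to one of the three trial conditions".
- Blinding: "participants will not be blind to treatment allocation due to the nature of the intervention".
- Interventions: "The therapist releases the modules gradually, two to three modules per week".
- Wait-list: "Participants allocated to the wait-list condition will receive assessments only at baseline, 6 weeks and 13 weeks".

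**The concern.** A moderator of a randomised effect is a variable that allocation cannot have changed. Patients with the same value in the two arms are then comparable, and the treatment contrast at each value remains a randomised contrast. A credibility score given in week 2 lacks this property. The iCT-PTSD participant rates iCT-PTSD and the iStress-PTSD participant rates iStress-PTSD. Each knows the allocation and has had access to the first modules. Equal scores in the two arms concern different treatments and may come from different kinds of patient.

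If the score also reflects how the patient is already doing, and does so more strongly in one arm, an interaction can appear although no pre-treatment characteristic modifies the effect. Moderator results are often used to suggest which patients suit which therapy, and this one would not support that use.

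**Working it through.** **Timing and role.** The plan gives no figure to reproduce, so the first check sets the statements side by side.

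1. Randomisation follows consent and precedes treatment (Allocation).
2. Participants know their arm (Blinding).
3. At two to three modules per week (Interventions), about 2 to 3 are released by the start of week 2 and 2 × 2 to 2 × 3 = 4 to 6 by its end. These are releases; completion is not documented.
4. The rating is made in week 2 (Treatment fidelity and credibility). The text describes no earlier rating. The schedule in Fig. 2 was not available in the text examined.
5. The wait-list is assessed at baseline, 6 and 13 weeks, so it has no rating during the wait. As a moderator, credibility could serve only the comparison of iCT-PTSD with iStress-PTSD.

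The variable is therefore post-randomisation by the protocol's own account.

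**How much it could matter.** All coefficients here are assumptions. Let U be early response (standard normal, same distribution in both arms), with no treatment effect and no moderation:

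- Credibility C = λ × U + 0.3 × arm + noise (SD 1), where the loading λ may differ by arm.
- Outcome Y = −0.6 × U + noise (SD 1), so Var(Y) = 0.36 + 1 = 1.36 and the SD is 1.166.
- Model fitted: Y on arm, C and arm × C.
- n = 79 per arm, from the Sample size section: 93 × (1 − 0.15) = 79.05.

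The within-arm slope of Y on C is β(λ) = −0.6λ / (λ² + 1):

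- β(0.3) = −0.18 / 1.09 = −0.165
- β(0.5) = −0.30 / 1.25 = −0.240
- β(0.8) = −0.48 / 1.64 = −0.293

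The spurious interaction is the difference in slopes: 0 for equal loadings, −0.075 for 0.3/0.5 and −0.128 for 0.3/0.8.

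The residual variance within an arm is 1.36 − β²(λ² + 1), which is 1.330, 1.288 and 1.220 for the three loadings. With s² the mean over the two arms, SE = √{s² [1/(1.09n) + 1/((λ² + 1)n)]}. The rejection rate is approximately Φ(z − 1.96) + Φ(−z − 1.96), where z = |difference| / SE.

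| Loadings | z at n = 79 | Approximate rejection rate | Simulated, n = 79 |
|---|---|---|---|
| equal (0.3/0.3 or 0.8/0.8) | 0 | 5% | 5.1% to 5.5% |
| 0.3/0.5 | 0.075 / 0.169 = 0.44 | 7.3% | 7.4% to 7.5% |
| 0.3/0.8 | 0.128 / 0.157 = 0.81 | 12.8% | 13.4% to 13.7% |

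With all 93 per arm, the 0.3/0.8 case gives z = 0.81 × √(93/79) = 0.88 and about 14% (simulated 14.8%).

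**Arm coefficient given credibility.** In the arm whose mean credibility is shifted by 0.3, E[Y | C] = β × (C − 0.3). The arm coefficient at C = 0 is therefore −0.3β although the true effect is zero. This is 0.3 × 0.165 = 0.050 for a loading of 0.3 in that arm and 0.3 × 0.293 = 0.088 for 0.8. Divided by 1.166, these are 0.04 and 0.08 SD. With no shift in mean credibility the bias is zero.

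**A second set-up** (93 per arm, a true arm effect of 0.35, credibility built from pre-treatment expectancy plus an arm-specific weight on early response) gave the same pattern. The rate was 4.6% to 5.3% with weights 0.3/0.3 and 0/0, and 12.6%, 21.3% and 42.4% with weights 0.5/0.2, 0.8/0.2 and 0.6/0. In every one of these scenarios, a moderator fixed before randomisation kept the rate between 4.7% and 5.7%.

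**The case against.** The strongest reply is that the protocol writes no interaction model. It calls these variables candidates, describes the work as exploratory and leaves details to an analysis plan that is not shown. A patient cannot judge a treatment's credibility before its rationale has been presented, so some delay belongs to the construct. The first three modules listed for each therapy are introductory, so material gains by week 2 are assumed. Unequal loadings are assumed too, and with equal loadings the interaction test keeps its nominal level.

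Much of this stands. It limits the size and consequence of the problem, but it does not reconcile role with timing. The protocol itself separates moderators from mediators, puts credibility with the moderators and fixes the rating at week 2, so leaving details to another plan does not remove the conflict. An associational reading of the week-2 score would be legitimate, but that is a different role from the one given. Nor does the argument need clinical gain by week 2: allocation is known, and the object being rated differs by arm.

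A reader might go further and infer that false moderation is likely, that participants have completed several modules when they rate, or that the trial's main result is affected. The documents support none of these. They give no credibility-response link in either arm and record module release only, and the primary PCL-5 comparison does not use credibility. The missing wait-list rating adds little, because the primary comparison is between the two therapies.

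**Conclusion.** The point holds as a mismatch between role and timing. As described, treatment credibility is a post-randomisation rating of the assigned treatment, and a condition-by-credibility interaction cannot be read as effect modification by a pre-treatment characteristic. That conclusion rests only on the protocol's text, subject to Fig. 2 showing no earlier rating.

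The size is conditional. In the main illustration the false-positive rate runs from no inflation (about 5%) through about 7% to about 14% as the arms' loadings diverge. The conditional arm coefficient is biased by 0 to 0.08 SD, depending on whether mean credibility differs. The higher rates, including those in the second set-up, need strongly unequal links that nothing in the protocol establishes, and should not be quoted as expected rates. The consequence is confined to an exploratory analysis.

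**What to change.** In the Process evaluation section, remove treatment credibility from the candidate moderators and state that moderators are limited to variables measured before randomisation. Keep the week-2 rating for two purposes:

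- a check that the two therapies were similarly credible, reported as a between-arm difference;
- an early process variable, possible mediator or within-arm predictor of outcome, with results described as associational.

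The separate analysis plan should use the same classification. The change costs wording only: no new data, no added burden on participants, and no effect on sample size or the primary analysis.

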#### Health economic evaluation

A full economic evaluation will be performed to compare the costs and effects of providing iCT-PTSD versus iStress-PTSD. The results of the economic evaluation will be expressed in costs per patient with a clinical improvement in PTSD symptoms and costs per QALY gained, using non-parametric bootstrapping and Cost-Effectiveness Planes and Cost-Effectiveness Acceptability Curves. Details will be specified in a separate health economic analysis plan.

### Monitoring

There are no stopping rules for the trial as it is a low-risk trial that does not use Investigational Medicinal Products (non-CTIMP).

#### Trial monitoring

The independent Trial Oversight Committee (TOC) will review the protocol and the statistical analysis plan, and regularly review recruitment rates, compliance with protocol, adverse events and effects, and completeness of data collection at least annually. Members are independent experts specialising in clinical trials, PTSD, or statistics and a service-user representative. The Trial Management Committee will meet monthly to oversee trial procedures and progress.

#### Safety

Adverse effects or events will be monitored throughout treatment (during weekly phone calls with the therapist) and follow-up (during independent assessments) [54]. Number and type of adverse events will be reported in the main trial publication. All serious adverse events (SAEs) must be reported immediately (and within 24 h of knowledge of the event) to the investigator and will be reported to the Research Ethics Committee (REC) that gave a favourable opinion of the study if they are ‘related’ (resulted from administration of any of the research procedures) and ‘unexpected’ in relation to those procedures. In addition to the usual SAE categories, for the purposes of this trial severe self-harm and harm to others must be reported. Therapists will be asked to notify the PI directly should they be concerned at any time that a participant has caused, or is likely to cause, significant harm to themselves. The therapist should conduct a risk assessment and also inform the participant’s GP. Therapists will be asked to inform the appropriate authorities directly should they become concerned at any time that a participant has, or is likely to cause significant harm to others. Assessors will be asked to complete a brief risk assessment if the participant discloses suicidal ideation and should discuss with a member of the clinical team what action to take.

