### Outcomes

#### Measures of symptoms and well-being

Details of assessment instruments and time points are found in the Standard Protocol Items: Recommendations for Interventional Trials (SPIRIT) Checklist (Fig. 2). The primary assessment is at 13 weeks (end of weekly phone calls/wait-list).

The primary outcome measure is the PTSD Checklist for *DSM-5* (PCL-5) [23], a standardised self-report measure of PTSD symptoms according to the *DSM-5* which is expected to yield the most complete data. Further measures of PTSD symptom severity include the IES-R [24], which is the PTSD measure used by IAPT services, and the Clinician Administered PTSD Scale for *DSM-5* (CAPS-5) [35], a semi-structured clinician-administered diagnostic interview for PTSD symptoms. The latter will be conducted by an independent trained assessor (a psychologist who is not one of the trial therapists) who will be unaware of the participant’s trial arm.

Measures of other symptoms and well-being include the Patient Health Questionnaire (PHQ-9) [25] to assess symptoms of depression; the Generalised Anxiety Disorder Scale 7-items (GAD-7) [26] to assess symptoms of anxiety; the WHO(Five) Well-Being Index [36] to assess psychological well-being; the Work and Social Adjustment Scale (WSAS) [27] to assess disability and interference with functioning; the Endicott Quality of Life Scale (QoL) [37] to assess quality of life and the Insomnia Sleep Index (ISI) [38] to assess sleep disturbance.

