### Data collection

Data will be collected from all participants, including those who discontinue treatment. Most of the outcome data will be collected via Qualtrics (anonymised by participant ID number), a widely used data collection software programme. If participants prefer, paper-and-pencil measures (anonymised by participant ID), these will be provided. Data for the process analyses will be captured online via the online therapy programmes (weekly measures). Access to the data will be restricted to named study personnel only and via a secure login (two-factor authentication).

The independent CAPS-5 assessors will receive comprehensive training in conducting and scoring the interview. Interrater reliability will be determined and discrepancies will be resolved by consensus.

In the event of source data being collected on paper, including the SCID-5 interview at the eligibility clinical assessment and the CAPS-5 interview at baseline (initial), 13, 26, 39 and 65 weeks, an exact copy of the anonymised data will be manually entered into the trial database by named study personnel, with the electronic data record being verified against the original paper record.

To aid retention, participants will be reimbursed £20 for completing each trial assessment at baseline, 6 weeks (including measures during treatment), 13 weeks, 26 weeks, 39 weeks and 65 weeks (see Fig. 2). They will not be paid for the clinical eligibility assessment and treatment.

Dropout, or premature termination from the study or treatment at any point after randomisation, will be recorded along with reason for discontinuation or termination. Participants can choose to withdraw from the trial intervention, withdraw from follow-up, withdraw from both aspects, or withdraw from both aspects and ask that previously collected data not be used. Their care in the NHS will not be affected at any time by declining to participate or withdrawing from the trial. A participant may be withdrawn from the intervention if they develop a condition which would exclude them from the study based on the eligibility criteria or a change in their clinical condition requiring urgent other treatment (e.g. the participant develops a psychotic disorder). Participants who withdraw/are withdrawn from the intervention part of the trial will continue in follow-up unless they withdraw their consent for this. Withdrawn participants will not be replaced.

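### Adverse events are sought at weekly therapist calls in both treatment arms but at one or two assessments on the wait-list, so treatment and wait-list counts are not comparable

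*Protocol article*

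**What the plan says.** The Safety section sets the collection method by period: "Adverse effects or events will be monitored throughout treatment (during weekly phone calls with the therapist) and follow-up (during independent assessments". It then commits to publication: "Number and type of adverse events will be reported in the main trial publication".

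The first channel exists only in the treatment arms. The Interventions section describes both online therapies as delivered "with the therapist support by messages within the programme, SMS and weekly phone calls". For the third arm, the Wait-list section states: "Participants allocated to the wait-list condition will receive assessments only at baseline, 6 weeks and 13 weeks". The period is the same length in all arms; under Measures of symptoms and well-being: "The primary assessment is at 13 weeks (end of weekly phone calls/wait-list".

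On what the assessments contain, the Data collection section places "the CAPS-5 interview at baseline (initial), 13, 26, 39 and 65 weeks", with no interview listed at 6 weeks, and adds: "Most of the outcome data will be collected via Qualtrics". The CAPS-5 interviewer is independent of treatment: "The latter will be conducted by an independent trained assessor (a psychologist who is not one of the trial therapists".

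**The concern.** The rule covers two periods, treatment and follow-up, and the wait is neither. Read literally, no channel is named for it. Read generously, with the wait counted under the independent assessments, the wait-list has that channel but not the weekly one. Either way, how often a participant is asked depends on the arm.

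This goes beyond a detail left to a fuller document. The article states a method, ties it to a contact that exists in two of three arms, and promises that the resulting numbers will be published. Nothing in the text warns that they come from unequal questioning. A table of events by arm would tend to show more on treatment than on the wait-list even if the true rates were equal, and could hide a true excess on the wait-list. An event missed during the wait may have no later chance of being recorded, because wait-list participants who no longer have PTSD at 13 weeks leave the trial.

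**Working it through.** The protocol gives no adverse-event rate or capture rate, so there is no planned figure to reproduce. The check has two parts.

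**1. Planned occasions to report an event, randomisation to week 13**

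Inputs: weekly calls in both treatments until week 13 (Interventions; Measures of symptoms and well-being); interview at week 13, none listed at week 6 (Data collection); no calls on the wait-list (Wait-list); arm sizes 93, 93 and 31 (Sample size).

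- Each treatment arm: 13 calls + 1 interview = 14 per participant.
- Wait-list: 0 calls + 1 interview = 1 per participant, or 2 if the 6-week assessment asks about events.
- Person-contacts: (93 + 93) × 14 = 2604 on treatment, against 31 × 1 = 31 on the wait-list (31 × 2 = 62 with week 6).
- iCT-PTSD against iStress-PTSD: 14 against 14.

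The 13 calls are one per week. The article states no number of calls, so this is a planned figure, not an observed one.

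**2. What this could do to recorded rates if the true rates are equal**

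Assumptions (not from the protocol): events fall evenly over the 13 weeks; each can be reported once, at the next contact; the chance of report halves every h weeks of delay, with h ranged from 2 to 26.

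For a contact at the end of an interval of L weeks, the share recorded is S(L) = [h / (L ln 2)] × (1 − 0.5^(L/h)).

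- Weekly contact: S(1). The week-13 interview coincides with the last call and adds nothing here.
- One contact at week 13: S(13).
- Contacts at weeks 6 and 13: (6/13) S(6) + (7/13) S(7).

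Example, h = 2: S(1) = [2/0.693] × (1 − 0.707) = 0.845; S(13) = [2/9.01] × (1 − 0.011) = 0.220; ratio 3.85.

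| h (weeks) | Weekly | Week 13 only | Weeks 6 and 13 | Ratio, weekly to one | Ratio, weekly to two |
|---|---|---|---|---|---|
| 2 | 0.845 | 0.220 | 0.397 | 3.85 | 2.13 |
| 4 | 0.918 | 0.397 | 0.599 | 2.31 | 1.53 |
| 8 | 0.958 | 0.600 | 0.764 | 1.60 | 1.25 |
| 13 | 0.974 | 0.721 | 0.844 | 1.35 | 1.15 |
| 26 | 0.987 | 0.845 | 0.918 | 1.17 | 1.08 |

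The ratio exceeds 1 in every row. Its size depends on the assumed half-life and on whether week 6 counts. Events that people remember well lie near the bottom of the table, and minor or transient ones near the top.

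**The case against.** The strongest reply is that the comparison most readers want is intact. The primary question is iCT-PTSD against iStress-PTSD, and these arms share the same calls and assessments. The objectives that involve the wait-list concern symptoms, well-being, disability, quality of life and sleep; none concerns adverse events, and the Safety section promises number and type, not a test between arms. All of this stands. It limits the point to treatment against wait-list. It does not remove it, because counts published for three arms invite the comparison whether or not a test is planned.

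A second reply is that the 6-week content is unknown. Fig. 2 is not shown, the full protocol is not at hand, and the sentence listing the interview times is about transcribing paper records, so it need not list every assessor contact. This also stands, and is why the count is given as 1 or 2. Two against about 14 is still unequal.

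A third reply is that safeguards reach every arm: serious events must be reported whenever they become known, assessors complete a risk assessment when suicidal ideation is disclosed, and the oversight committee reviews adverse events at least annually. A reader might infer that the wait is unmonitored and that harm during it would be missed. The text does not support that. What it supports is weaker detection, since these safeguards act only on what is disclosed or already known.

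A reader might also infer that treated participants who leave the intervention escape collection. They stay in follow-up unless they withdraw consent for it, and events are collected there. Nothing in the document shows that these are the people who worsened.

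**Conclusion.** The point holds for each treatment arm against the wait-list over weeks 0 to 13: about 14 planned occasions to report an event against 1 or 2. That count follows from the text, apart from the unseen content of the 6-week assessment. The possible distortion, a recorded rate about 1.1 to 3.9 times higher on treatment with equal true rates, rests on an assumed recall model and could be small.

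It would be too strong to conclude that the trial can say nothing about harm. Relative harm between the two therapies, 93 against 93 planned participants, is not affected on this point, and neither is the primary efficacy analysis. The flaw is worth correcting because a result promised for the main publication would otherwise mislead in one of its comparisons, and correction is cheap.

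**What to change.** - Name the 13-week wait in the Safety section and state how events are recorded during it.
- Put one identical short adverse-event form in the existing 6- and 13-week assessments for all three arms.
- Base any treatment against wait-list statement in the main publication on that common source, weeks 0 to 13. List events found only through therapist calls separately, without a wait-list comparison.
- Report by arm the proportion whose PCL-5 worsened from baseline to 13 weeks, with the definition of worsening fixed in advance. These data are already collected on the same schedule in every arm.

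If it is too late to add items (the Trial status section gives recruitment until 31 March 2020), the reporting rule still applies, restricted to events recorded at assessments common to all arms, and so does the PCL-5 count.

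The cost is a slightly longer form at two assessments, and fewer events in the common-source comparison than in the full log. How participants are clinically monitored during the wait is for the trial team to state and to reconcile with the Wait-list section; this point concerns only measurement and reporting.
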